## Protocol Synopsis

|                             |                                                                                                                                                                                                                                                                                                                                                                                                                                                                                                                                                                                                                             |
|-----------------------------|-----------------------------------------------------------------------------------------------------------------------------------------------------------------------------------------------------------------------------------------------------------------------------------------------------------------------------------------------------------------------------------------------------------------------------------------------------------------------------------------------------------------------------------------------------------------------------------------------------------------------------|
| Study code                  | EPO                                                                                                                                                                                                                                                                                                                                                                                                                                                                                                                                                                                                                         |
| Protocol title              | Does erythropoietin improve outcome in very preterm infants?                                                                                                                                                                                                                                                                                                                                                                                                                                                                                                                                                                |
| Study design                | Multicentre, placebo-controlled, prospective, randomised, double-blind (verum:placebo = 1:1) Study                                                                                                                                                                                                                                                                                                                                                                                                                                                                                                                          |
| Planned sample size         | Total number 420 preterm infants                                                                                                                                                                                                                                                                                                                                                                                                                                                                                                                                                                                            |
| Calculation of case numbers | 176 cases per group (2-sided alpha 0.05, power 0.8)                                                                                                                                                                                                                                                                                                                                                                                                                                                                                                                                                                         |
| Study duration              | Scheduled starting date: 01/2006
Prospective total duration of study 24 months + 24 mths follow-up
Study duration (clinical part) / patient max. 16 weeks until 40. th week of gestation                                                                                                                                                                                                                                                                                                                                                                                                                   |
| Question                    | Does erythropoietin reduce brain, eye, lung and gut damage and ameliorate the neurodevelopmental outcome in preterm infants?                                                                                                                                                                                                                                                                                                                                                                                                                                                                                                |
| Primary Objective           | Mental development at 24 months (Bayley II)                                                                                                                                                                                                                                                                                                                                                                                                                                                                                                                                                                                 |
| Secondary Objectives        | 
 
1. Incidence of intracranial haemorrhage
 
2. white matter disease (periventricular leucomalacia)
 
3. septicaemia
 
4. necrotising enterocolitis
 
5. persistent ductus arteriosus (PDA)
 
6. bronchopulmonary dysplasia
 
7. retinopathy
 
8. Length of stay in hospital
 
9. Cerebral volume at 40 postmenstrual weeks (MRI)
 
10. Weight, length and head circumference at 40 postmenstrual weeks and 24 months after term
 
11. Incidence of visual, hearing and motor impairment at 24 months
 
 |
| Inclusion Criteria          | 
 
1. Infants born between 260/7 and 316/7 gestational weeks
 
2. Postnatal age less than 3 hours
 
3. Informed parental consent (preferably obtained before birth)
 
                                                                                                                                                                                                                                                                                                                                                                      |
| Exclusion Criteria          | 
 
1. Genetically defined syndrome
 
2. Severe congenital malformation adversely affecting life expectancy
 
3. Severe congenital malformation adversely affecting neurodevelopment
 
4. A priori palliative care
 
5. Intracranial haemorrhage grade 2 or more
 
                                                                                                                                                                                                                                                                                  |
| Investigational drug        | Human erythropoietin, intravenous application Dosage: 3000 U/kg of body weight, Administered three times, at 3 hours, 12 to 18 hours and 36 to 42 hours after birth.                                                                                                                                                                                                                                                                                                                                                                                                                                                        |
| Comparison therapy          | NaCl 0.9%, same administration route and volume as investigational drug                                                                                                                                                                                                                                                                                                                                                                                                                                                                                                                                                     |

## 1.6 Time table

| Point(s) of time
Action         | Before start of study | In Hospital |             |                             |                | Follow-up         |                                     |
|------------------------------------|-----------------------|-------------|-------------|-----------------------------|----------------|-------------------|-------------------------------------|
|                                    |                       | Day 1 -3    | Day 7 to 10 | Every two gestational weeks | Discharge home | Gestation week 40 | 24 months corrected for prematurity |
| Inclusion criteria                 | •                     |             |             |                             |                |                   |                                     |
| Exclusion criteria                 | •                     |             |             |                             |                |                   |                                     |
| Demographic data                   | •                     |             |             |                             |                |                   |                                     |
|                                    |                       |             |             |                             |                |                   |                                     |
| Vital signs                        |                       |             |             |                             |                |                   |                                     |
| Continuous monitoring  | •                     | •           | •           | o                           |                |                   |                                     |
| Laboratory                  |                       |             |             |                             |                |                   |                                     |
| Blood count            | •                     | o           | •           | o                           |                |                   |                                     |
| Clinical chemistry     | o                     | o           | o           | o                           |                |                   |                                     |
| Placenta Histology                 |                       | o           |             |                             |                |                   |                                     |
| Ventilation/CPAP            |                       |             |             |                             |                |                   |                                     |
| Respiratory support                | •                     | •           | •           | •                           |                |                   |                                     |
| Ventilation parameters             | •                     | •           | •           | •                           |                |                   |                                     |
| Diagnostics                 |                       |             |             |                             |                |                   |                                     |
| Epo concentration      | •                     |             |             |                             |                |                   |                                     |
| Cerebral ultrasound                | •                     | •           | •           | •                           | •              |                   |                                     |
| Chest X-ray                        |                       | •           | o           | o                           | o              |                   |                                     |
| Brain MRI                          |                       |             |             |                             |                | o                 |                                     |
| Serum, csf cultures                | o                     | o           | o           | o                           |                |                   |                                     |
| Therapy                     |                       |             |             |                             |                |                   |                                     |
| Antibiotics                        | •                     | •           | •           | •                           |                |                   |                                     |
| Catecholamines                     | •                     | •           | •           | •                           |                |                   |                                     |
| other medication       | •                     | •           | •           | •                           |                |                   |                                     |
| Study medication            |                       |             |             |                             |                |                   |                                     |
| administration of investigat. drug |                       | •••         |             |                             |                |                   |                                     |
| Adverse events                     |                       | •           | •           | •                           | •              |                   |                                     |
| Serious adverse events             |                       | •           | •           | •                           | •              |                   |                                     |
| Confirmation of completeness       |                       |             |             |                             | •              |                   | •                                   |

- compulsory (for medication, adverse events etc indicate „no“ if none), o optional
- Continuous monitoring: heart rate, pulse oximetry, (optional: transcutaneous pO2 and pCO2, arterial blood pressure, cerebral oxygenation with Near infrared Spectroscopy [NIRS] optional)
  - Blood counts: haematocrit; leucocytes, thrombocytes and differential blood count only when medically indicated
  - Clinical chemistry: Na, K; creatinine, urea (only when medically indicated))
  - Epo concentration in umbilical cord serum
  - Other medication: aminophylline, caffeine, insuline, indomethacine or ibuprofen, steroids etc.

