### **Undesirable effects**

Serious, life-threatening side effects have not been observed to date, neither within the scope of approved application of Epo in adults, nor within the established therapy in preterm infants to prevent anaemia.

During and at least 24 hours after injection heart rate, arterial saturation (pulse oximetry) or transcutaneous pO2 and (arterial) blood pressure will be monitored and the infant will be observed clinically.

Haematological examination including haematocrit, haemoglobin, red and white cell count and thrombocytes will be done at day 7 to 10.

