### **Adverse Events (AE), Definition**

Adverse events are taken to be any general lack of well-being, symptoms of illness, laboratory parameters outside the normal range and other impairments observed within the context of a clinical study. This applies regardless of any causal connection with the investigational study drug administered.

Any event not attributable to the category „serious“ (see section 8.4) is considered an adverse event (AE).

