### **How will individual findings be collected and documented?**

Data will be entered on-line from the patients' files (original data, source data) in each participating center. The following data will be collected on the basis of the patient file, depending on ventilation time:

- Apgar and CRIB score
- Ventilation (ventilation route, ventilation type, FiO2.)
- Blood gas analysis (pH, pO2, pCO2, BE, HCO3, SaO2)
- Blood counts (haemoglobin, leukocytes, thrombocytes) clinical chemistry: Na, K, creatinine, urea
- Pathogen detection until 36 week of gestation age
- Weight, head circumference at birth and at day 7-10 and 36 /7 postmenstrual weeks

Additionally, the following materials will be forwarded to the appropriate addresses for testing:

- Cord serum (EPO concentration)
- Continuous NIRS monitoring data before and after first dose for assessment of changes in tissue oxygenation index (only selected infants in Zurich).
- MRI at 40 weeks of gestation (optional)

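### The protocol gives two different rules for white cell and platelet counts at day 7 to 10: unconditional in section 6.3, on medical indication in the time table

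*Protocol*

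**What the plan says.** Section 6.3 (Undesirable effects) sets out safety monitoring: "Haematological examination including haematocrit, haemoglobin, red and white cell count and thrombocytes will be done at day 7 to 10". No condition is attached, so it reads as applying to every infant.

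The time table in section 1.6 has a row for blood count. It carries the compulsory mark before the start of study and at day 7 to 10, and the optional mark at days 1 to 3 and at the two-weekly visits. The legend explains the symbols: "compulsory (for medication, adverse events etc indicate „no“ if none), o optional". The note to that row defines its content. It names haematocrit first and then, after a semicolon, "leucocytes, thrombocytes and differential blood count only when medically indicated".

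Section 10.2 lists, among the data to be entered, "Blood counts (haemoglobin, leukocytes, thrombocytes) clinical chemistry: Na, K, creatinine, urea". It introduces the list with "The following data will be collected on the basis of the patient file, depending on ventilation time".

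Section 8.3 counts "laboratory parameters outside the normal range" as adverse events. Section 8.1 has adverse events sent to the sponsor at day 10 and monitored continuously by the safety board, which is to stop the trial if complications are in significant excess under EPO at p < 0.01.

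**The concern.** The two texts describe the same visit but require different tests. A centre working from the time table can satisfy it and still fall short of section 6.3, while a centre working from section 6.3 measures everyone. Nothing ranks one text above the other.

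This matters for safety data because an abnormal count is itself an adverse event under section 8.3, and a count that is never taken cannot become one. Under the time-table note, whether a low platelet or abnormal white cell count is found depends on a clinical decision made after randomisation. The safety board would then see laboratory events whose completeness depends on which text each centre followed. An analysis plan cannot repair this later, because values that were not measured cannot be recovered.

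**Working it through.** No sample size, power or alpha figure in the protocol bears on this point, so there is none to reproduce. The check is a comparison of the texts.

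**Step 1. Components required at day 7 to 10.**

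| Component | Section 6.3 | Time-table note |
|---|---|---|
| Haematocrit | unconditional | unconditional |
| Haemoglobin | unconditional | not named |
| Red cells | unconditional | not named |
| White cells | unconditional | on medical indication |
| Platelets | unconditional | on medical indication |
| Differential | not listed | on medical indication |

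Of the five components in section 6.3, the texts agree on one (haematocrit) and conflict directly on two (white cells, platelets). The note is silent on the other two. The differential is not in conflict, because section 6.3 does not ask for it.

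**Step 2. Is the note read correctly?** The semicolon after haematocrit separates it from the items that follow, so the condition attaches to those items. The next note, on clinical chemistry, has the same form: sodium and potassium stand alone, and creatinine and urea follow a semicolon with the same condition.

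**Step 3. Does the compulsory mark resolve it?** No. The mark makes the blood count compulsory, and the note then says what the blood count contains.

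**Step 4. Does another section resolve it?** Section 10.2 names leukocytes and thrombocytes, but as data taken from the patient file, with no visit given. That fits either rule. The diagram in section 1.7 mentions a blood count at assessment A2, but its bracket breaks off in the text available, so it cannot be relied on either way.

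**Step 5. What selective testing could do (illustration only; all inputs assumed).** Let p be the true proportion of infants with an abnormal count, a the probability of testing an infant with an abnormal count, and b that of testing an infant with a normal count. Then

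proportion abnormal among those tested = p·a / (p·a + (1 − p)·b).

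Take a = 0.9 and b from 0.5 down to 0.3:

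- p = 5%: 0.045/0.520 = 8.7%, up to 0.045/0.330 = 13.6%
- p = 10%: 0.090/0.540 = 16.7%, up to 0.090/0.360 = 25.0%
- p = 20%: 0.180/0.580 = 31.0%, up to 0.180/0.420 = 42.9%

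The denominators give the share of infants tested, from 33% to 58%. Over all infants the count errs the other way: at p = 10%, 0.10 × 0.9 = 9% are found. Selective testing therefore overstates the rate among those tested and understates it among all randomised. If everyone is tested (a = b = 1), both equal p.

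**The case against.** The best defence is that section 6.3 is the specific text for this visit, while the note covers a whole row with four marked time points, two of them optional. A centre could reasonably take section 6.3 as governing day 7 to 10, and no selection would then arise. That stands as a limit: the consequence follows only where the note is followed. It does not remove the conflict, because the protocol leaves each centre to choose.

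Four stronger readings are tempting, and the protocol does not support them.

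- A reader might infer that the comparison between arms is biased. The trial is double-blind, so knowledge of the arm should not drive testing. Bias would need EPO to change which infants acquire an indication. That is possible, but nothing in the protocol shows it.
- A reader might infer that the adult risks named in section 8.1 would go undetected. Polycythaemia is covered by haematocrit, which both texts require. Thrombosis is a clinical event, and adverse-event recording is compulsory from day 1 to discharge. A platelet count is at most an indirect marker.
- A reader might want to express the problem as lost power for a platelet comparison. The protocol plans no such comparison, and neither platelets nor white cells appear in its endpoint lists, so a power figure would rest wholly on invented inputs.
- A reader might take section 10.2 as a third conflicting rule. It is compatible with both.

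That the tested infants would be sicker is a fair inference from testing on indication, but the protocol does not say so.

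**Conclusion.** This is an internal inconsistency in current text. Sections 1.6 and 6.3 give different rules for white cells and platelets at a compulsory safety visit, and the note omits haemoglobin and red cells, which section 6.3 requires. Where centres follow the note, laboratory adverse events would be incompletely ascertained, in a subset selected after randomisation and possibly to a different degree by centre.

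The size cannot be taken from the protocol, because it gives no rate of medical indication and no expected rate of abnormal counts. The illustration shows the direction and plausible scale of the distortion under its assumptions and is not an estimate for this trial. The point concerns completeness of safety data. It does not affect the primary endpoint, any listed secondary endpoint or the sample size. The conflict itself rests on no assumption; the consequence assumes that at least some centres work from the time table.

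**What to change.** Reconcile section 1.6 (the blood count row and its note) with section 6.3, so that one stated rule for the day 7 to 10 count applies to every infant at every centre. Which testing rule is right is for the sponsor to decide. If the monitoring that section 6.3 already states is to be kept, the note has to be aligned with section 6.3 for that visit.

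The same edit should say what the compulsory count before the start of study contains. The note makes white cells and platelets conditional there too, so a change confined to day 7 to 10 could leave those values without a complete baseline. The list in section 10.2 can then refer to the agreed rule and name the visit.

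The cost is the wording of one note and a cross-reference. If section 6.3 is the rule kept, it adds no day 7 to 10 test beyond those that section already states. For infants already past that visit, reports to the safety board should give the number tested, by arm and centre, beside any count of abnormal values.
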